### Trial design {8}

This investigator-initiated prospective randomized parallel groups monocentric controlled trial is designed to enroll 200 patients. There is no blinding because cannulas are easy to distinguish.

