### Strategies to improve adherence to interventions {11c}

Intervention is a single procedure\ event and does not require repetition, therefore adherence is not a feature of intervention delivery.

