## Statistical methods

### Statistical methods for primary and secondary outcomes {20a}

The primary and secondary outcomes will be evaluated using the *χ*^2^ test in terms of the difference in approaches of cannula insertion between groups in the number of punctures and the failure rate of the cannulas (failure rate is defined as the proportion of cannulas requiring reinsertion within 5 days after insertion). RR and 95% confidence interval of successful venous cannulation will be also calculated. The primary endpoint is the number of attempts to successful cannulation determined by the number of skin punctures. More attempts are associated with complications. As a secondary endpoint, the failure rate is calculated from the ratio of cannulas that did not fail to cannulas that failed for any reason in each group, up to the first 5 days postoperatively. This data is obtained from the patient protocol (Fig. 2). Primary and secondary outcomes will be reported as frequencies and percentages. For our tertiary outcome, to compare differences between the intervention groups (time required for cannula insertion, number of cannulas used, A-DIVA scoring system, etc.), *t*-test for independent groups or Mann–Whitney U test will be used, if data are not normally distributed. The effect of the intervention on outcome variables will be determined by using paired *t*-test or Wilcoxon signed-rank test for data obtained at baseline and for 5 days of the study. Other endpoints include portion of long PVCs that are able to ensure blood draw up to 5 days postoperatively, time needed to insert PVC in each group, reinsertion of PVC needed in both groups for any reason. All this data is recorded in the study protocol.

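### One sentence assigns the intervention effect to paired before-after tests, which contain no comparison of the arms and conflict with the between-group tests named beside it

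*Protocol article*

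**What the plan says.** The Trial design section {8} describes a "prospective randomized parallel groups monocentric controlled trial is designed to enroll 200 patients". The statistical methods section {20a} starts consistently with that design. The primary and secondary outcomes go to a chi-square test "in terms of the difference in approaches of cannula insertion between groups in the number of punctures and the failure rate of the cannulas", with a risk ratio and 95% confidence interval for successful cannulation. Tertiary outcomes, with insertion time, number of cannulas used and the A-DIVA score as examples, go to a t-"test for independent groups or Mann–Whitney U test will be used, if data are not normally distributed".

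The next sentence changes the comparison. It opens with "The effect of the intervention on outcome variables will be determined by using paired" and offers two procedures: the parametric test for matched observations and its rank-based alternative. The data to be matched are named at its end, in the words "signed-rank test for data obtained at baseline and for 5 days of the study". The sentence does not restrict which outcome variables it covers, and it does not call the result descriptive, secondary or within-group.

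**The concern.** In a randomised parallel-group trial, the effect of the intervention is the difference between the arms. A paired t-test or signed-rank test compares each patient with himself or herself at another time. Whether it is run in one arm, in each arm separately or on all patients pooled, it never sets ultrasound against palpation, so the protection given by randomisation is not used.

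The section therefore contains two incompatible accounts of how the effect is obtained, and the unsuitable one is the sentence that uses the words effect of the intervention. The trial is unblinded. An analyst following that sentence could report a within-arm p-value as evidence for ultrasound when it reflects only what happens to any cannula over five days.

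**Working it through.** The protocol gives no figure for the paired analysis, so there is none to reproduce. The check has three parts.

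**1. Is there an arm contrast?** A paired test uses d = (later value − baseline value) for each patient and tests whether d is centred on zero. Treatment arm does not enter the formula. The Sample size section {14} gives no support to such a test either: it compares the risk of an unsuccessful prick between groups, 20% under the standard technique against 5% with ultrasound.

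**2. Is there a baseline to pair with?**
- Section {11c} describes the intervention as a single procedure that "does not require repetition, therefore adherence is not a feature of intervention delivery".
- The Outcomes section {12} says that attempts, redirections and insertion time are recorded during the procedure.
- The participant timeline {13} shows baseline variables and the primary outcome once each, both at Day 1, and the secondary outcome at Days 2–4 and Day 5. No measurement of an outcome before insertion is scheduled.

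Attempts, insertion time and redirections therefore have one value per patient and nothing to pair it with. The A-DIVA score could be taken before insertion, but no repeat is stated and it already has a between-group test.

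**3. What would the test show where it could be run?** Cannula function is the natural candidate for day-by-day data. Assume that a cannula can only go from working to failed and that there are 100 patients per arm (200 split equally). Every non-zero difference then has the same sign. The two-sided exact sign-test p-value with k failures is 2 × 0.5^k:
- k = 5: 2 × 0.5^5 = 0.0625, not significant.
- k = 6: 2 × 0.5^6 = 0.031, significant at 0.05.

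Six failures in an arm are enough. With X ~ Binomial(100, p), the probability of at least six is:

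| Assumed failure by day 5 | P(X ≥ 6) |
|---|---|
| 5% | 38% |
| 10% | 94% |
| 20% | over 99.9% |

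These probabilities apply to each arm separately and require no difference between the arms.

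A continuous outcome behaves in the same way. Assume two identical arms of 100, unit standard deviation, correlation 0.5 between baseline and follow-up, and a shift over time of 0.3 SD common to both arms. The SD of the change is √(1 + 1 − 2 × 0.5) = 1, and the non-centrality is 0.3 × √100 = 3. The paired t-test in one arm then rejects with probability of about 84% (a simulation of 4,000 trials gave 83%). In the same simulation a between-arm test of the change rejected in about 5%, as it should with no true effect.

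**The case against.** The strongest reply is that the between-group tests are already in place, and this is correct. The primary and secondary outcomes have a chi-square test with a risk ratio and interval, the tertiary outcomes have independent-group tests, and the objectives and sample size are comparative. A reader might infer from the paired sentence that the trial's main result will come from before-after tests, or that no between-arm analysis exists. The document does not support that: no confirmatory endpoint depends on the sentence.

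Three further limits stand.
- **No baseline.** This is established for attempts, insertion time and redirections. It is not established for every item. Baseline in the timeline may mean Day 1 status, the list of tertiary variables is open-ended, and the record form is not shown. Where no baseline exists, the sentence cannot be carried out and does no harm. Where a Day 1 state serves as baseline, the false signal in part 3 arises. These are separate cases.
- **The control arm.** A reader might infer that control patients are left out. The sentence does not say so. The accurate criticism is that the arms are never compared.
- **The numbers.** They price a hypothetical analysis. Cannula failure is assigned to the chi-square test, the sentence names a paired t-test or signed-rank test rather than a sign test, and the protocol gives no day-5 failure rate. Its 20% concerns complications of insertion. It would be wrong to infer that a spurious result is planned or certain.

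One might also say that only within-group change is meant. In that case the sentence is mislabelled, and relabelling it is the remedy. A fuller analysis plan could add detail, but it would not make this published statement correct.

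**Conclusion.** The sentence is wrong as written. A paired test on baseline and 5-day data cannot determine the effect of ultrasound guidance against palpation, it conflicts with the between-group tests in the same section, and for attempts, insertion time and redirections it has nothing to pair. The conflict follows from the text alone and rests on no numerical assumption.

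The size of the possible error does rest on assumptions: one-way failure, 100 cannulas per arm, and 10% to 20% failing by day 5. Within-arm significance would then appear with probability of about 94% to over 99.9% whether or not the arms differ. At lower failure rates the probability falls, to 38% at 5%.

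Severity is moderate. The defect is one conflicting sentence in a plan whose primary and secondary analyses are already between-group.

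**What to change.** Delete the sentence on paired tests. Alternatively, keep it as a descriptive within-arm summary, name the variables and the two time points it covers, and state that it is not used for inference about the intervention. In either case add that every intervention effect is the between-arm contrast, reported with a 95% confidence interval and tested with the between-group methods already named in section {20a}.

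A between-arm model for daily data, such as time to cannula failure or a repeated-measures model with arm, day and their interaction, is optional. The defect does not require it, because the secondary endpoint is a 5-day proportion that already has a between-group test.

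The cost is one sentence of text, with no additional patients, data or change in conduct.

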### Interim analyses {21b}

Not applicable as no interim analyses are planned.

### Methods for additional analyses (e.g., subgroup analyses) {20b}

When studying with several groups, we will combine these groups appropriately; in other words, we will analyze different intervention versus control subgroups and create simple pairwise comparisons using the same statistical analysis methods that have already been described for categorical or metric (continuous) quantities in the “Data collection and statistical methods” section.

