**Methods:**

This investigator-initiated prospective randomized monocentric controlled trial is designed to randomly allocate 200 patients undergoing elective primary total joint arthroplasty of hip or knee to one of two groups as follows: Group C (control group) – peripheral venous cannula insertion by palpation or Group USG (intervention) – cannula insertion by ultrasound-guided vascular access. Our primary endpoint is to compare the number of attempts for ultrasound-guided insertion of the peripheral venous cannula with common palpation insertion of the peripheral venous cannula in overweight/obese patients (BMI ≥ 25). The secondary endpoint is a failure rate of the peripheral venous cannula to administer intravenous therapy up to 5 days postoperatively. Tertiary endpoints include a portion of long PVCs that are able to ensure blood draw up to 5 days postoperatively, time needed to insert PVC in each group, number of needle tip redirections in both groups, and reinsertion of PVC needed in both groups for any reason.

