### Sample size {14}

The estimate for the final sample size was based on the expected drop-out rate and the objective and design of the study. This trial assumes a comparison of the effect on outcome variables in peripheral vein insertion in the USG group and palpation-inserted peripheral venous cannula as the control group. In overall, we hypothesize that it will take fewer attempts to insert the cannula into a vein with the USG technique (USG: 1 vs. C: 1–3), corresponding to a reduction in time of ≥ 3 min (clinically relevant indicator) for successful cannulation in the USG group. When calculating the sample size, based on our experience and literature data, we assumed a 20% risk of complications inserting the cannula into a vein in the standard way, 5% as a probability of a Type I error (α < 0.05), and the power of the test 90% (β = 0.10). Theoretically, we also accepted a 5% risk failure of a first insertion of a cannula into a vein in the USG group. The sample size calculation was based on the result of the risk ratio (RR) between groups as % of complications (unsuccessful prick) with cannula insertion into the peripheral veins [9]. The adequate sample size of 162 patients was calculated as described previously [10], increased by 20% for the case unforeseeable circumstances (technical error, data loss, poor patient cooperation, etc.) and rounded ≅ 200.

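### The subgroup paragraph is worded for several groups in a two-arm trial, and the pairwise tests it fixes cannot show whether the effect of ultrasound differs between subgroups

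*Protocol article*

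**What the plan says.** The paragraph on additional analyses {20b} in the protocol article is a single sentence. It opens "When studying with several groups, we will combine these groups appropriately" and explains this as follows: "we will analyze different intervention versus control subgroups and create simple pairwise comparisons using the same statistical analysis methods" already described for categorical or continuous quantities. The section title it cites does not appear in the article under that name. The only tests described are in Statistical methods for primary and secondary outcomes {20a}, so I take those to be meant.

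Section {20a} says: "The primary and secondary outcomes will be evaluated using the" χ² test, adding a risk ratio with 95% confidence interval for successful cannulation. For the tertiary variables it gives a t-test "for independent groups or Mann–Whitney U test will be used, if data are not normally distributed", and it mentions paired tests for change over time. Nothing in {20a} or {20b} compares a treatment effect between subgroups.

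The abstract says that patients are allocated after "elective primary total joint arthroplasty of hip or knee to one of two groups as follows", namely palpation (C) and ultrasound (USG). Trial design {8} describes parallel groups. No subgroup factor is named in the objectives, outcomes, sample size or statistics sections.

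**The concern.** There are two problems in one sentence.

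First, combining several groups has no object here. With one intervention arm and one control arm there is nothing to combine.

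Second, the sentence stands under a subgroup heading, speaks of subgroups, and fixes a method: pairwise intervention-versus-control comparisons with the main tests. A test inside one subgroup asks whether ultrasound works there. It does not ask whether ultrasound works better there than elsewhere, which is normally why a subgroup is examined. That question is natural in this trial. The background section {6a} argues that palpation becomes very difficult at higher BMI while ultrasound is largely unaffected, which is a statement about effect modification. A-DIVA scoring is also listed in {20a}.

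If subgroup results appear only as separate tests, a significant result beside a non-significant one is easily taken for a difference in effect. At this sample size that pattern is common even when the effects are identical.

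**Working it through.** **1. Inputs.**
- Control risk, from Sample size {14}: "we assumed a 20% risk of complications inserting the cannula into a vein in the standard way".
- Ultrasound risk, from the same section: "we also accepted a 5% risk failure of a first insertion of a cannula into a vein in the USG group".
- α = 0.05 and power 90%, with sidedness not stated; 162 evaluable patients, raised to about 200.
- My assumptions: 1:1 allocation, two-sided tests within subgroups, two independent subgroups with the same true effect.

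**2. The plan's own figure.** The plan gives no figure for subgroups. Its nearest figure is 162, from

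n per arm = [z(α)·√(2p̄q̄) + z(β)·√(p₁q₁ + p₂q₂)]² / (p₁ − p₂)²

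with p̄ = 0.125, √(2 × 0.125 × 0.875) = 0.4677 and √(0.16 + 0.0475) = 0.4555.
- One-sided: (1.645 × 0.4677 + 1.282 × 0.4555)² / 0.15² = 81.4, so 82 per arm and 164 in total, close to 162.
- Two-sided: (1.960 × 0.4677 + 1.282 × 0.4555)² / 0.15² = 100.1, so 101 per arm and 202 in total.

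So 162 is consistent with 20% versus 5% as a one-sided calculation. The present point does not depend on that figure.

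**3. What the text fixes.** Each test in {20a} compares the two arms, or two time points within patients. None has a term for the difference between two treatment effects. Applied within subgroups, they give one p-value per subgroup and, for successful cannulation, one risk ratio with its interval per subgroup.

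**4. Power within one subgroup.** Take 200 patients in two equal subgroups, so 50 per arm in each.
- Normal approximation: Φ[(√50 × 0.15 − 1.960 × 0.4677) / 0.4555] = Φ(0.316) = 0.624.
- Exact enumeration of the uncorrected χ² test: 0.664.

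**5. Chance that exactly one of the two tests is significant.** With power π in each subgroup this is 2π(1 − π).

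| Patients per arm per subgroup | Method | π | 2π(1 − π) |
|---|---|---|---|
| 50 | exact | 0.664 | 2 × 0.664 × 0.336 = 0.446 |
| 50 | approximation | 0.624 | 0.469 |
| 40 (about 162 evaluable) | exact | 0.574 | 2 × 0.574 × 0.426 = 0.489 |
| 40.5 (162 evaluable) | approximation | 0.533 | 0.498 |

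A simulation of 400,000 trials gave 0.446 at 50 per arm and 0.489 at 40.

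**6. Other assumptions.** For unequal subgroups at N = 200 the chance is π₁(1 − π₂) + π₂(1 − π₁), by the approximation:
- One third and two thirds: 0.456 × 0.249 + 0.751 × 0.544 = 0.522.
- One quarter and three quarters: 0.357 × 0.201 + 0.799 × 0.643 = 0.586.

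With no effect in either of two subgroups it is 2 × 0.05 × 0.95 = 0.095.

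**7. Interaction test for comparison.** The same simulated data were tested with z = (d₁ − d₂)/√(V₁ + V₂), where d is the risk difference in each subgroup and V its variance. This falsely signalled a difference in 5.4% of trials at 50 per arm and 5.6% at 40.

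**The case against.** The strongest reply is that the sentence may not describe subgroup analysis at all. Its second half explains its first, so it can be read as generic wording for reducing several arms to pairwise contrasts. With two arms that is just the main comparison. This stands as far as it goes: the sentence is ambiguous. But that reading leaves the paragraph without an application in this trial, and the heading and the word for subgroups point the other way. Neither reading gives a suitable subgroup method.

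A reader might infer something stronger, namely that the plan's method itself produces spurious subgroup differences, or that such differences will be reported. The article does not support this. It names no subgroup, announces no comparison between subgroups, and nowhere says that a difference will be inferred from one significant and one non-significant test. The 45% is the frequency of a pattern under assumed subgroups. It becomes an error rate only if someone draws that inference.

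It is also fair that for successful cannulation the cross-referenced methods supply a risk ratio with 95% CI, so the output would not be p-values alone. Estimates with intervals are better to look at, but they are still not a test of difference.

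Finally, a list of subgroup factors and model details may belong to an analysis plan or full protocol that is not shown. Their absence is not held against the article. The point rests on the method that the article does state.

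**Conclusion.** The point holds as a minor one. The paragraph is unclear, its several-groups wording does not fit a two-arm trial, and the method it fixes cannot show whether the effect of ultrasound differs between subgroups.

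The size is illustrative: about 45% discordant significance at 50 per arm per subgroup and about 49% at 40, against about 5% false signals from an interaction test. This rests on two equal subgroups with the same 20% versus 5% effect, two-sided 5% tests and 1:1 allocation. Unequal subgroups give roughly 52% to 59% by the approximation, and no effect at all gives about 10%. The primary and secondary comparisons between arms are not affected.

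**What to change.** Delete the wording about combining several groups and replace the paragraph with, for example:

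*The trial has two arms. Any difference in effect between subgroups is judged by a treatment-by-subgroup interaction term in a regression model for the outcome. It is reported with the effect estimate and 95% CI in each subgroup, and it is exploratory.*

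The choice of subgroup factors may be left to the statistical analysis plan, provided it is made before the data are analysed. The effect scale of the interaction (risk ratio or risk difference) should be named there too. If control risk differs between subgroups, as the BMI argument implies, the answer can depend on the scale.

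The cost is a change of wording and a little more analysis work. The interaction test will have low power with about 200 patients, so a non-significant result will not show that effects are equal. That is acceptable for an exploratory analysis. No new data or patients are needed.

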### Methods in analysis to handle protocol non-adherence and any statistical methods to handle missing data {20c}

Not all processes set up in the study deviate from the design of the randomized controlled clinical trial. When analyzing data, if any qualitative or metric data is found, we will first contact a team member who records or measures the data to supplement the missing data, if at all possible, while analyzing the reasons why the data is missing. We will use all available SPSS applications to check/analyze data completeness. In addition, SPSS statistical programs can evaluate and process incomplete data sets correctly (each analysis uses only cases without missing values for all variables and for all analyses). Therefore, we will not artificially attribute any missing values and we will take into account the missing data in the interpretation of the results. Patients with a large amount of missing data will be excluded from the final statistical analysis.

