### Eligibility criteria {10}

Inclusion criteria are (1) age group of 18–75 years, (2) body mass index > 25, and (3) primary hip or knee arthroplasty. Exclusion criteria are as follows: (1) reoperation of arthroplasty, (2) mental disorder, (3) sepsis, (4) protocol non-compliance, (5) pregnancy, and (6) patient refusal or no informed consent or both. Interventions are performed by anesthetists trained in UGVA.

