### Criteria for discontinuing or modifying allocated interventions {11b}

The procedure may be performed with or without a tourniquet following the insertion manual (Fig. 1). The method should be discontinued after two unsuccessful attempts and another experienced practitioner should be sought. If such a practitioner is not available it has to be marked in the protocol as “failure” with a note “no experienced practitioner available.” Another researcher makes notes into the study protocol (Fig. 2).

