### Plans to promote participant retention and complete follow-up {18b}

Participants are studied only up to 5 days or discharge from the hospital, whichever comes first. The study doesn’t require any extra actions or active collaboration from patients. If the patient deviates from intervention protocols, we will use data of the patient up to the timepoint of deviation if eligible; if not, the patient will be excluded. Exclusion probability is low due to the short period of observation and low to none patient active collaboration.

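### The stated complete-case rule and open-ended exclusions can remove randomised patients from a primary endpoint that was already recorded at the procedure

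*Protocol article*

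**What the plan says.** All references are to the protocol article.

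- **Missing data {20c}.** SPSS is said to process incomplete data correctly because "each analysis uses only cases without missing values for all variables and for all analyses". The next sentence, opening with a word of consequence, concludes that "we will not artificially attribute any missing values and we will take into account the missing data in the interpretation of the results". The parenthesis describes software, but the conclusion drawn from it makes it the plan.
- **Exclusion for incompleteness {20c}.** "Patients with a large amount of missing data will be excluded from the final statistical analysis". No threshold is given, nor who decides.
- **Deviators {18b}.** "we will use data of the patient up to the timepoint of deviation if eligible; if not, the patient will be excluded". Eligible is not defined here. The same section ends observation at day 5 or at discharge if that is earlier.
- **Eligibility {10}.** The exclusion criteria include "4) protocol non-compliance", with no statement of when it is applied.
- **Primary endpoint {20a}.** "The primary endpoint is the number of attempts to successful cannulation determined by the number of skin punctures". The Outcomes section {12} has it recorded during the procedure, and the participant timeline {13} places it on Day 1.
- **Blinding {17a}.** There is none.

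No section states that all randomised patients are analysed in the arm to which they were allocated.

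**The concern.** The primary endpoint is complete almost by construction: punctures are counted while the cannula is placed. The stated rules nevertheless make a patient's presence in the primary comparison depend on other things. These are completeness on other variables, some collected on Days 2 to 5 and cut short by discharge; an unquantified view of how much missing data is too much; and an undefined view of whether a deviator is eligible. In an unblinded trial the last two judgements can be made by people who know both the arm and the number of punctures.

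At stake is the comparability that randomisation provides. If removals are unrelated to arm and outcome, the cost is precision. If they are related to both, the risk ratio and the type I error of the main test are affected as well.

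**Working it through.** **1. The plan's own size.** Inputs from Sample size {14}: failure risk 20% (control) and 5% (ultrasound), alpha 5%, power 90%, 162 patients, plus 20%. Equal allocation is my assumption. Pooled-variance formula per arm, with mean risk 0.125:

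n = [z(alpha) × √(2 × 0.125 × 0.875) + z(power) × √(0.20 × 0.80 + 0.05 × 0.95)]² / 0.15²

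- One-sided 5%: [1.645 × 0.4677 + 1.282 × 0.4555]² / 0.0225 = 81.4, so 82 per arm and 164 in all. The unpooled version gives 158. Both lie close to 162.
- Two-sided 5%: 100.1, so 101 per arm and 202 in all.
- Allowance: 162 × 1.2 = 194.4, rounded to 200.

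The scenarios below therefore use 100 per arm. The documents give no missing or exclusion rates, so **every loss figure below is an assumption**.

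**2. Loss unrelated to outcome (20% versus 5%, two-sided 5%).**

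Power = Φ{[0.15 − 1.96 × √(0.21875/n)] / √(0.2075/n)}

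| Patients per arm | Power |
|---|---|
| 100 | (0.15 − 0.0917)/0.0456 = 1.28, so 0.90 |
| 90 | 0.87 |
| 80 | (0.15 − 0.1025)/0.0509 = 0.93, so 0.82 |
| 60 | 0.70 |

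Small gaps add up under a rule that spans all variables. With 10 variables, each missing independently in 2% of patients, 0.98^10 = 0.82 of patients are complete and power is about 0.83. At 1% per variable, 0.90 are complete (power 0.87); at 5%, 0.60 (power 0.70).

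**3. Loss related to outcome, no true difference (20% in both arms).** Suppose a share f of ultrasound-arm failures is removed and no one else. The observed ultrasound risk is 0.20(1 − f)/(1 − 0.20f).

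| f | Removed per 100 | Observed risk | Expected RR | Two-sided type I error (simulated) |
|---|---|---|---|---|
| 0 | 0 | 0.200 | 1.00 | 0.051 |
| 0.10 | 2 | 0.184 | 0.92 | 0.060 |
| 0.25 | 5 | 0.15/0.95 = 0.158 | 0.79 | 0.117 |
| 0.50 | 10 | 0.111 | 0.56 | 0.394 |

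**4. Direction.** Under the design rates, removing a quarter of ultrasound failures (1.25 per 100) moves the RR from 0.25 to 0.19. Removing a quarter of control failures instead (5 of 20) gives a control risk of 15/95 = 0.158 and an RR of 0.05/0.158 = 0.32. The same kind of rule can exaggerate or dilute the effect, and nothing in the documents says which would occur.

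**The case against.** The case for the plan has real substance.

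- **The wording may just be clumsy.** The quoted parenthesis begins as though deletion were per analysis, and only its ending extends it to all variables. If per-analysis deletion was meant, the text needs correcting. The separate exclusions in {20c} and {18b} would remain.
- **The default for deviators is retention.** Section {18b} keeps data up to the deviation where possible and expects few exclusions. Section {20c} first tries to recover missing values from the person who recorded them, and {19} adds double data entry. These steps lower the likely loss. They do not say what happens to the patients who remain incomplete, and a low expected number is not a safeguard.
- **The sample size already allows for losses of 20%.** That allowance protects numbers, not comparability, and 200 patients only just give 90% two-sided power with nobody lost.
- **Analysis sets are often left to an SAP.** That is fair for a threshold or a sensitivity analysis. The point here rests on rules that the article states; the missing as-randomised commitment matters because nothing overrides them.

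Three stronger readings are tempting, and the documents do not support them. A reader might infer that the rule deletes every control patient, because blood draw is an endpoint for long cannulas only. That field is not applicable to controls rather than missing, and {20a} plans between-arm tests. A reader might infer that the non-compliance criterion can only be known after allocation. It stands among criteria screened on Day −1 and may mean expected inability to comply. A reader might also infer that difficult insertions become deviations. Section {11b} says "The method should be discontinued after two unsuccessful attempts and another experienced practitioner should be sought", which makes stopping part of the protocol, and it records the case as a failure if no such practitioner is available.

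**Conclusion.** The concern holds in this form: read as written, {20c} and {18b} allow patients with a recorded primary outcome to be dropped from the primary comparison, either for later gaps or by undefined judgement in an unblinded trial. No statement elsewhere commits to analysing everyone as allocated.

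A link between exclusion and both arm and outcome is possible but not documented, and the size and direction of bias cannot be computed from the documents. The figures are scenarios resting on 100 per arm, equal allocation, a two-sided 5% test and assumed exclusion rates. About 5 ultrasound-arm failures removed under no true difference gives an expected RR near 0.79 and type I error near 0.12. A random loss of 20% at the design rates takes power from about 0.90 to about 0.82. Since the outcome is captured at the procedure, nearly all of this risk is avoidable. The rules should be corrected before outcome data are examined, because a later choice of who is analysed would be made with the results visible.

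**What to change.** 1. State that the primary analysis includes all randomised patients in the arm allocated, and that procedures recorded as failures under {11b} count as failures.
2. Replace the parenthesis in {20c} with per-endpoint handling: each endpoint uses every patient with that endpoint recorded, and neither a later gap nor a not-applicable field removes anyone from the primary analysis.
3. Remove the exclusions for much missing data ({20c}) and for deviation ({18b}) from the primary analysis. If a per-protocol set is wanted, define it and use it for sensitivity only.
4. In {10}, state that the non-compliance criterion applies only to screening before allocation and is no ground for removal after randomisation.
5. Optionally, add a best-case and worst-case sensitivity analysis for any missing primary value.

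The cost is revised wording in three sections and, with item 5, one extra table. No change to recruitment, data collection or sample size is needed for this point.
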